
We therefore propose that self-control training will only have a substantive effect on behavioral outcomes if individuals are motivated to change their behavior. Participants whose self-control capacity has been trained, but have little or no motivation to reduce their alcohol consumption are less likely to direct the increased self-control capacity gleaned from training toward that particular behavior. They may direct their efforts toward behaviors to which they are more motivated instead. We therefore expect that the combined manipulation of self-control training and motivational imagery-based intervention components, namely, mental simulations, to be more effective in changing behavior than either of the components alone. Importantly, the factorial design adopted in the present study permits the evaluation of the independent and synergistic effects of each of the intervention components on alcohol consumption. In addition, we expect the intervention to be highly acceptable for use in public health promotion campaigns due to its low response burden and highly practical, accessible, and cost-effective means of delivering the intervention.

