### Participants

Participants will be undergraduate students from a large University in Western Australia. Students will be eligible to participate if that are 18 years or older and non-abstinent with respect to alcohol consumption to be eligible to participate in the study. Participants will be excluded if they are heavy or dependent drinkers as identified by the Fast Alcohol Screening Test (FAST) [103]. Participants will be recruited using email circular and notice board advertisements distributed throughout the University and from a dedicated participant pool for undergraduate psychology students incentivised by course credit or a prize draw for shopping vouchers. The study is described as an intervention to reduce alcohol consumption. Assuming a medium effect size for mental simulation interventions on behavior reported by Pham and Taylor [31] (*d* = 0.56) and an effect size of similar magnitude for the effects of self-control resource training reported in Hagger et al.’s [81] meta-analysis (*d* = .62), a power analysis using G*Power v3.1 [104] setting power at .80 and alpha at .05, estimates that we will require a total sample size of between 120 and 144 participants with between 30 and 36 participants in each intervention group. The variation in the sample size estimate is due to the use of the two different effect sizes to compute the power analysis, each of which gives a slightly different result.

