Data on the primary dependent variable of alcohol consumption will be analysed using a 2 (mental simulation: mental simulation vs. no mental simulation) × 2 (self-control training: challenging vs. easy) factorial between-participants analysis of covariance (ANCOVA) with alcohol consumption at follow-up as the dependent variable and baseline alcohol consumption and trait self-control as covariates. The analysis permits the main and interactive effects of mental simulation and self-control training intervention components. We predict statistically-significant main effects of medium size of mental simulation and self-control training on alcohol consumption, but also expect a statistically-significant, medium-sized interaction effect such that participants receiving the mental simulation and challenging self-control training components will report significantly lower levels of alcohol consumption than participants receiving either of the intervention components alone and participants that received neither manipulation.

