## Discussion

Excessive consumption of alcohol among young people has been recognized as a significant public health issue due to its association with numerous health, social, and economic problems [1]. Undergraduate students tend to be a particularly high-risk group as they frequently engage in risky patterns of alcohol consumption such as binge-drinking [5-7]. Behavioral interventions have been shown to be effective in reducing alcohol consumption in young people e.g., [14,108], but few have reported the theoretical basis of the intervention and its components, tested the independent and interactive effects of the techniques aimed at reducing alcohol consumption, and identified they key mediators of the intervention effects.

The present study aims to conduct a four-week theory-based intervention using leading behavior-change techniques to reduce alcohol consumption at follow-up among undergraduate students. The intervention will adopt motivational and self-control training behavior-change techniques derived from psychological theory and use a randomized-controlled factorial design to examine the unique and interactive effect of each technique in on alcohol consumption. According to theory, we hypothesize that participants receiving both intervention components should exhibit the lowest levels of alcohol consumption at follow-up relative to participants receiving each of the intervention conditions alone and participants receiving neither of the components. In addition, the research will also evaluate the theoretically-relevant mediating variables that explain the effect of the motivational and self-control training intervention components on alcohol consumption. Specifically, we expect the motivational intervention component to be mediated by social cognitive variables including intentions, attitudes, and motivation and the self-control intervention to be mediated by perceived self-control resource availability.

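### The interaction term is made to carry the claim that the combination beats each component alone and neither; it tests synergy correctly but does not test that ordering

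*Protocol article*

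**What the plan says.** The primary analysis (protocol article, Data analysis) is one 2 × 2 ANCOVA of follow-up alcohol consumption, with baseline consumption and trait self-control as covariates. Its output is described thus: "The analysis permits the main and interactive effects of mental simulation and self-control training intervention components". The section predicts two medium main effects and a significant interaction, also medium. It spells out the form of that interaction as an ordering: the group given both components "will report significantly lower levels of alcohol consumption than participants receiving either of the intervention components alone and participants that received neither manipulation".

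The ordering also appears elsewhere. The current research expects the combination "to be more effective in changing behavior than either of the components alone". The Discussion gives it as the hypothesis without mentioning an interaction: "participants receiving both intervention components should exhibit the lowest levels of alcohol consumption at follow-up", compared with each single-component group and the group receiving neither.

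Synergy is stated as well. The current research says that the two components are expected to interact, and that training should matter only for people who are motivated to change.

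The sample size (Participants) uses d = 0.56 for simulation and d = 0.62 for training, "setting power at .80 and alpha at .05", and arrives at a "total sample size of between 120 and 144 participants with between 30 and 36 participants in each intervention group".

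**The concern.** An interaction asks whether the effect of one component changes in the presence of the other. The ordering asks whether one cell mean lies below each of three others. Neither answer implies the other. Two components that simply add make the combination best with an interaction of exactly zero. A non-zero interaction, in turn, does not show that the combined cell is below every other cell.

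The main effects do not close the gap, because each averages over the other factor and never sets the combined cell against a single-component cell.

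At stake is the claim that the Discussion puts forward. If the ordering is judged through the interaction, the trial can fail to support a combination that really is best. Comparisons examined only after a significant interaction would have the same problem.

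**Working it through.** **Inputs.** From Participants: d = 0.56 and 0.62, alpha 0.05, power 0.80, n = 30 to 36 per cell. From Data analysis: four cells and two covariates, so error df = N − 6. Assumed: residual SD 1, two-sided tests, no dropout and no gain from covariates unless stated. Lower is better.

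**The plan's own figure.** With f = d/2 in a noncentral F calculation (four groups, two covariates), 3 numerator df gives N = 144 for d = 0.56 and N = 118 for d = 0.62, or 120 at 30 per cell. With 1 numerator df the results are 103 and 84. The stated 120 to 144 therefore matches a 3-df test across the four cells. It was not derived from the 1-df interaction or from a cell comparison.

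**The two quantities.**
- Interaction = (both − simulation only) − (training only − neither); SE = √(4/n), which is 0.365 at n = 30 and 0.333 at n = 36.
- Cell contrast = both − one other cell; SE = √(2/n), which is 0.258 and 0.236.

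For contrasts of equal size the interaction has twice the variance. At d = 0.62, power is 0.39 (n = 30) and 0.455 (n = 36) for the interaction, against 0.66 and 0.74 for a cell contrast.

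**Additive case, step by step.** Cell means (neither, simulation, training, both) are 0, −0.56, −0.62, −1.18. The interaction is (−1.18 + 0.56) − (−0.62 − 0) = 0. The ordering is true. Contrast power at 30 / 36 per cell:
- against simulation only (difference −0.62): 0.66 / 0.74
- against training only (difference −0.56): 0.58 / 0.66
- against neither (difference −1.18): 0.995 / 0.999
- all three together, by simulation: 0.46 / 0.55

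**Joint results by simulation, 30 / 36 per cell.**

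| Scenario (neither, simulation, training, both) | Interaction significant as predicted | All three contrasts succeed |
|---|---|---|
| Additive: 0, −0.56, −0.62, −1.18 | 2.5% / 2.5% | 46% / 55% |
| Training works only if motivated: 0, −0.56, 0, −1.18 | 39% / 45% | 66% / 74% |
| Only the combined cell benefits, d = 0.56: 0, 0, 0, −0.56 | 33% / 39% | 33% / 42% |
| Only the combined cell benefits, d = 0.62: 0, 0, 0, −0.62 | 39% / 45% | 43% / 53% |
| Both main effects d = 0.56, interaction f = 0.25: 0.31, 0.25, 0.25, −0.81 | 77% / 85% | 96% / 99% |

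The last row takes the medium interaction as f = 0.25; the protocol gives no figure for it.

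**If the contrasts are examined only after a significant interaction.** The ordering is then reached in about 2.5% of additive trials. In the second scenario it is reached in 36% / 43% rather than 66% / 74%.

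**Covariate gain.** With an assumed baseline correlation of 0.7 and 36 per cell, the interaction rejects (two-sided) in 5% of additive trials against 88% for the three contrasts. In the second scenario the figures are 73% and 95%. Adjustment raises power generally but leaves the 2:1 variance ratio unchanged.

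**The case against.** The strongest reply is that the interaction is the right test of something the authors plainly claim. The current research sets out a moderation hypothesis, and the ordering can be read as the predicted shape of that interaction. Under pure additivity the synergy prediction is false, so a low rejection rate is correct behaviour. All of this stands. A reader might infer that the interaction is the wrong test and should be replaced; the documents do not support that. The additive case shows only that the ordering claim, which the Discussion makes in its own right, can be true while the interaction is silent.

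Second, follow-up comparisons may sit in a fuller plan that is not shown. That is fair, and missing detail is not the point here. The point rests on what Data analysis does say: it hangs the ordering on the interaction. Follow-up tests conditional on that interaction would not repair this.

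Third, the main effects are also tested. In the additive case both are significant in 79% / 88% of trials at 30 / 36 per cell, so the trial would not be silent about benefit. They still do not compare the combination with either component alone.

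Fourth, a reader might infer that a significant interaction could be passed off as proof of the ordering. For a sub-additive interaction this does not hold, because its direction would contradict the prediction. A misleading result in the predicted direction is possible: means 0, +0.5, +0.5, 0 give a significant interaction in 77% / 85% of trials with a combination no better than neither. But this needs each component alone to increase drinking, against everything that the protocol predicts. It shows the logical gap, not a likely outcome.

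**Conclusion.** The point holds in a limited form. The interaction tests synergy properly; it does not test whether the combined cell is below each of the other three, and Data analysis attaches that claim to it. At the protocol's own effect sizes and cell sizes, the cost ranges from almost the whole chance of showing the ordering (2.5% against 46% to 55% if effects add) to nothing (about 33% either way if only the combined cell benefits at d = 0.56 with 30 per cell). Under the protocol's own theory that training needs motivation, it is 39% to 45% against 66% to 74%.

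A reader might infer that the interaction is always the less powerful route. It is not: the third scenario shows no gain at 30 per cell, and the comparison could reverse if single components did harm.

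The figures assume residual SD 1, equal cells, two-sided 0.05, no dropout and no covariate gain; the scenarios are illustrations built from the stated d values. The mismatch between test and claim does not depend on any of them. It should be corrected, because the ordering is a central hypothesis and the correction needs no new data.

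**What to change.** Keep the interaction, with its confidence interval, as the test of synergy. Add three pre-specified contrasts from the same ANCOVA: combined against simulation only, combined against training only, and combined against neither. Test each two-sided at 0.05 and report all three with confidence intervals whether or not the interaction is significant. Claim the ordering only if all three are significant in favour of the combination. Because every one must succeed (an intersection-union rule), no alpha adjustment is needed.

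State the power of this joint claim openly. At 30 to 36 per cell it is modest: 46% to 55% if effects add, without covariate gain. State also which hypothesis the sample size is meant to serve.

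The cost is one added paragraph. The model, data and planned sample size stay as they are.

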We will also conduct mediation analyses to evaluate the effectiveness of the intervention components on alcohol consumption. This will be conducted using moderated linear regression analyses with indirect effects reproduced using Preacher, Curran, and Bauer’s [110] asymptotic bootstrapped algorithms and the bias-corrected bootstrap confidence interval to assess the statistical significance of the effects [111]. Specifically, we will develop binary dummy-coded variables to represent the effects of the mental simulation (1 = received mental simulation, 0 = received irrelevant visualization strategy) and self-control training (1 = received challenging Stroop task, 0 = received easy Stroop task) interventions with an additional variable computed to represent the interaction of the two. The primary outcome variable, follow-up alcohol consumption, will be regressed on these coded variables in the first instance to ascertain direct effects. This will be followed by analyses including multiple mediators of the effects including residualized change scores for the baseline and follow-up measures of the theory of planned behavior variables (intentions, subjective norms, attitudes, perceived behavioral control) and motivation as mediators of the mental simulation intervention and residualized change scores in state perceived self-control between baseline and follow-up as a mediator of the effect of the self-control training intervention. The unstandardized effects and confidence intervals will be used as input for Preacher et al.’s [110] bootstrapped algorithm computational tool to compute the indirect effects. We predict statistically-significant, medium-sized multiple mediation of the effects of the mental simulation intervention on follow-up alcohol consumption by the theory of planned behavior and motivational change scores and significant mediation of the effect of self-control training on alcohol consumption by state self-control change scores. Trait self-control will be included in the analyses as a control variable.

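### In the mediation regressions, 0/1 coding with a product term makes each intervention coefficient an effect at the other factor's control level, not the main effect tested in the ANCOVA

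*Protocol article*

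**What the plan says.** The mediation part of Data analysis (protocol article, Methods) fixes the coding: "we will develop binary dummy-coded variables to represent the effects of the mental simulation" and, likewise, of the training. Mental simulation is "1 = received mental simulation, 0 = received irrelevant visualization strategy" and training is "1 = received challenging Stroop task, 0 = received easy Stroop task", "with an additional variable computed to represent the interaction of the two". Follow-up alcohol consumption "will be regressed on these coded variables in the first instance to ascertain direct effects". Mediators are added after that: change scores in the planned-behavior variables and motivation for mental simulation, and change in state self-control for training. The plan predicts "significant mediation of the effect of self-control training on alcohol consumption by state self-control change scores", without limiting this to either level of mental simulation. It calls the approach a moderated regression but does not write out the equations for the mediators.

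Two other places bear on this. The ANCOVA paragraph of the same section tests main effects and the interaction, and predicts that all three are significant and of medium size. The current research (Background) states that "self-control training will only have a substantive effect on behavioral outcomes if individuals are motivated to change their behavior".

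**The concern.** The coded variables are introduced as standing for the effects of the two interventions. Under this coding they do so only at the zero level of the other factor. The simulation coefficient compares two easy-Stroop cells, and the training coefficient compares two irrelevant-visualization cells. If there is an interaction, as the protocol expects, the ANCOVA and the mediation models will report different quantities under the same name.

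Training is the more exposed of the two. Its coefficient on drinking is estimated in the half that receives no motivational component, where the protocol's own theory expects little effect on drinking. A near-zero value there would agree with the theory but could be read as training having failed. The protocol presents the identification of mechanisms as one of the study's contributions, so it matters which effect is being decomposed.

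**Working it through.** **Inputs.** Both 0/1 codings and the product term come from Data analysis. The effect sizes (d = 0.56 for simulation, d = 0.62 for training), alpha 0.05, power 0.80 and N of 120 to 144 (30 to 36 per cell) come from Participants. Equal cells and two-sided tests are assumed. Effects are in residual SD units and given as absolute sizes.

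**The plan's sample size.** With f = d/2, four groups and a 3-df omnibus F test, d = 0.56 gives N = 144, and d = 0.62 gives 118, or 120 in four equal groups. This reproduces the stated range. A 1-df main-effect test needs only 103 and 84. The sample size was therefore not derived for main effects, simple effects or mediation; it is used below only for its d values and cell sizes.

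**What the coefficients estimate.** Let μ(s,t) be the cell mean for simulation s and training t, in the model Y = b0 + b1·S + b2·T + b3·S·T.

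- b1 = μ(1,0) − μ(0,0): simulation among easy-Stroop participants.
- b2 = μ(0,1) − μ(0,0): training among irrelevant-visualization participants.
- b3 = μ(1,1) − μ(1,0) − μ(0,1) + μ(0,0).
- The main effect of training is ½{[μ(0,1) − μ(0,0)] + [μ(1,1) − μ(1,0)]} = b2 + b3/2, so b2 is the main effect minus half the interaction. The same holds for b1.

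**Standard errors.** With n per cell, the variance of b1 or b2 is 2σ²/n under 0/1 coding and σ²/n under −0.5/+0.5 coding.

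| n per cell | 0/1 | −0.5/+0.5 |
|---|---|---|
| 36 | √(2/36) = 0.236 | √(1/36) = 0.167 |
| 30 | √(2/30) = 0.258 | √(1/30) = 0.183 |

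**Power for one coefficient (total effect or a single path), no interaction.** Noncentral t with N − 6 df; noncentrality d√N/2 for the main effect and d√(N/8) for the 0/1 coefficient.

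| d | N | Main effect | 0/1 coefficient |
|---|---|---|---|
| 0.56 | 144 | 91.6% | 65.5% |
| 0.62 | 144 | 95.9% | 74.3% |
| 0.62 | 120 | 92.0% | 66.3% |

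**With an interaction.** The protocol says only that it is medium, so the sizes here are assumptions, expressed as the difference between the two simple effects. For a main effect of 0.56 at N = 144, a difference of 0.25 gives a coefficient of 0.56 − 0.125 = 0.435 (power 45%), and 0.50 gives 0.56 − 0.25 = 0.31 (power 26%). If training changes drinking only alongside simulation, b2 for drinking is 0.

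**The indirect effect of training.** Two simulations of 5,000 runs at 36 per cell, with assumed path sizes and the product term carried into the mediator regression:

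- *Training raises self-control only with simulation* (by 1.12, so 0.56 on average; mediator slope −0.5 throughout). The mean indirect effect is 0.00 under 0/1 coding and −0.28 under centred coding. If the product is left out of the mediator regression, 0/1 coding also gives −0.28.
- *Training raises self-control by 0.56 in both halves, but self-control reduces drinking only with simulation* (slope −0.5 there, 0 otherwise). The mean indirect effect is −0.14 under either coding, with SDs of about 0.080 and 0.067, a ratio of 1.2. The true conditional indirect effects are 0 without simulation and 0.56 × (−0.5) = −0.28 with it. Neither coding recovers these unless the mediator slope may differ by simulation.

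**The case against.** The strongest objection concerns the harm to the mediation result. A reader might infer that the mediated effect of training is being tested exactly where the theory says it is absent. The document does not support that. The current research says that unmotivated participants are less likely to direct their improved self-control at drinking; it still speaks of capacity gained from training. That places the moderation on the step from self-control to drinking, which is the second simulated case, where the mean indirect effect is the same under both codings. The expected zero applies to the total or direct coefficient on drinking. This part of the objection stands.

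A reader might also take the fall from 92% to 66% as a loss of power for mediation. It is not: those figures are for a total effect or one path, and in the second case the indirect effect loses much less precision. Nor does the analysis discard half the data. Two of four cells are contrasted, but the residual variance, covariate slopes and mediator slope use everyone.

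It is also true that the mediator equations are not written out. That the product enters them is the natural reading of a moderated regression on the coded variables, but not a stated fact. Finally, both codings are the same fitted model, and the main effect can be recovered as the coefficient plus half the product coefficient. This limits the severity. It does not remove the mismatch, because the stated plan labels the 0/1 coefficients as the intervention effects and mentions no such step.

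**Conclusion.** The point holds for the regression of follow-up drinking, where the coding and the product are explicit. Each arm coefficient is the effect at the other factor's control level: main effect minus half the interaction, with a standard error √2 times larger. It equals the ANCOVA main effect only if the interaction is zero, and the protocol predicts otherwise. For training, the protocol's theory implies a coefficient on drinking near zero in that half. The point extends to the mediator regressions only if the product is carried into them.

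It does not follow that the indirect effect of training is zero, that mediation loses 26 percentage points of power, or that the primary analysis is at risk. The ANCOVA, the model fit and the interaction test are unaffected. The exact √2 rests on equal cells; the power figures also assume the protocol's d values on the residual SD scale. This is a defect of moderate weight in a secondary analysis, and should be corrected before the data are analysed.

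**What to change.** Code both factors −0.5/+0.5, form the interaction as the product of these codes, and use this coding in every mediation regression, stating that the product enters the mediator equations too. The arm coefficients are then main effects that correspond to those in the ANCOVA.

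Report the indirect effect of each component at each level of the other. For training, add a term for state self-control change by mental simulation to the drinking regression, so that the mediator slope can differ between the simulation groups. Recoding alone does not test the hypothesis as the protocol states it.

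The cost is a recode and one extra model term, with no additional data or participants. The level-specific indirect effects will be less precise than an averaged one, and the report should say so.

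### The mediation plan reads direct effects off a regression without mediators; that model gives total effects, so the label and the model it points to need correcting

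*Protocol article*

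**What the plan says.** The mediation paragraph of the Data analysis section (Protocol article) codes each component 0/1 and adds a product term, "with an additional variable computed to represent the interaction of the two". Follow-up consumption "will be regressed on these coded variables in the first instance to ascertain direct effects". Only after that do the mediators enter: "This will be followed by analyses including multiple mediators of the effects including residualized change scores". These scores cover the theory of planned behavior variables and motivation for mental simulation, and state self-control for the training component. Indirect effects come from a separate step, a "bootstrapped algorithm computational tool to compute the indirect effects". On covariates, the paragraph says: "Trait self-control will be included in the analyses as a control variable".

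The paragraph also states what it expects to find: "We predict statistically-significant, medium-sized multiple mediation of the effects of the mental simulation intervention on follow-up alcohol consumption", and likewise mediation of the training effect by state self-control. The term total effect is not used, and no other place in the article says which model supplies the direct effect.

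**The concern.** In a mediation analysis, the direct effect is the counterpart of the indirect effect: what remains of a component's effect once the mediators are held fixed. A model without mediators cannot isolate that part. It returns the direct and indirect parts together.

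Mechanism is a declared aim. The Background promises mediators that explain how the components work, and the Discussion counts identifying mechanisms among the study's contributions. An analyst who follows the sentence literally would set the total effect beside the indirect effect and call it direct. A component whose effect runs entirely through its mediators would then seem to keep a full-sized unmediated effect, so full mediation would look partial. This matters most when mediation is present, which is what the plan predicts.

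**Working it through.** **Inputs.** The order of the models, the 0/1 coding with a product term, and the separate computation of indirect effects come from the Data analysis section. The value d = 0.56 is the mental simulation planning effect in the Participants section. The plan gives no figure for a total, direct or indirect effect and no share mediated, so there is no mediation figure to reproduce. Every share and path value below is an assumption.

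**Step 1: the identity.** Write

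- first step: Y = i1 + c·X + covariates, with no mediators;
- mediator models: Mj = i2j + aj·X + covariates;
- later model: Y = i3 + c'·X + Σ bj·Mj + covariates.

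Here X stands for the two dummies and their product. For ordinary least squares on the same participants and covariates, c = c' + Σ aj·bj holds exactly for each of the three condition terms. The first step therefore estimates c, the total effect. The direct effect is c', and the gap c − c' is the whole indirect effect.

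**Step 2: numerical check.** Simulated 2 × 2 data were used: N = 144 (the upper end of the planned sample), one mediator per component, a trait covariate, and 2,000 runs per scenario. The entries are means for the mental simulation coefficient. A negative value means less drinking.

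| Assumed c', a, b | Case | c (first step) | c' (direct) | Indirect |
|---|---|---|---|---|
| −0.28, 0.7, −0.4 | same sign | −0.562 | −0.281 | −0.281 |
| 0, 0.8, −0.7 | full mediation | −0.554 | 0.005 | −0.559 |
| −0.56, 0, −0.4 | no mediation | −0.563 | −0.568 | 0.005 |
| −0.84, 0.7, 0.4 | opposite sign | −0.558 | −0.840 | 0.282 |

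The largest deviation from the identity in any run was about 1e-14, which is rounding error. Nearly the same first-step coefficient (about −0.56) appears in all four rows, while the direct effect ranges from about zero to −0.84. The first step by itself cannot tell these cases apart.

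**Step 3: illustrative size.** With same-sign mediation, direct = total × (1 − share mediated). Assume a total effect of 0.56.

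- 30% mediated: 0.56 × 0.7 = 0.39; ratio of total to direct 1 / 0.7 = 1.4.
- 50% mediated: 0.56 × 0.5 = 0.28; ratio 1 / 0.5 = 2.0.
- 70% mediated: 0.56 × 0.3 = 0.17; ratio 1 / 0.3 = 3.3.

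**Step 4: what the first-step coefficient refers to.** With 0/1 codes and a product term, the mental simulation coefficient is that component's effect among participants on the easy Stroop task. The training coefficient is the effect among those given the irrelevant visualization. These are simple effects at the other factor's control level. In a balanced design, the average main effect is the first-order coefficient plus half the product coefficient. The plan predicts an interaction, so the two should differ, and 0.56 is not a forecast of what the first step will return.

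**The case against.** The strongest reply is that this is one misused word. Regressing the outcome on the conditions first and adding mediators afterwards is a usual sequence, and direct may be meant loosely, as the effect of the conditions before anything else enters. The correct model is already planned: "This will be followed by analyses including multiple mediators of the effects". Indirect effects are bootstrapped separately and not obtained by subtraction, so the label cannot bias them. The mediation predictions concern indirect effects only, and the primary ANCOVA is a separate analysis.

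Most of this stands. A reader might infer that the unmediated part is bound to be overstated, or that the same reduction will be counted twice. The article supports neither. It does not say that the first-step coefficient will be added to the indirect effect, compared with it, or used for a proportion mediated. Overstatement also requires mediation of the same sign as the direct effect, which the plan expects but cannot guarantee.

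The reply does not rescue the sentence. In a paragraph on indirect effects, direct effect has a fixed meaning, and the text assigns it to the one model that cannot supply it. Nothing tells the analyst to take it from the later models. Nor is this a detail that a condensed article leaves to a fuller plan: the article states which model is to be used for direct effects, and the statement is wrong.

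**Conclusion.** The point holds as an error of label and of assigned model, with a conditional risk of misreporting. The first-step coefficients are total effects. Reported as direct effects, they are wrong by exactly the indirect effect: too large in the predicted same-sign case, too small with opposite-sign mediation, and unchanged with none. The exact identity assumes linear models fitted to the same participants and covariates.

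The 1.4-, 2.0- and 3.3-fold ratios are illustrations. They rest on an assumed total effect of 0.56 and assumed mediated shares, none of which the plan states for this regression, and they should not be read as an expected bias. What is affected is the reported direct effect in a secondary analysis that serves a declared aim. The tests of indirect effects, the primary ANCOVA and the sample size are not.

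**What to change.** Reword the mediation paragraph so that:

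- the regression without mediators is said to estimate the total effect of each condition term;
- direct effects are taken from the planned models that include the mediators;
- total, direct and indirect effects are reported on the same participants and with the same covariates, so that they add up;
- first-order coefficients are described as simple effects at the other factor's control level, for as long as 0/1 coding with a product term is used.

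The cost is a sentence or two. The change needs no new data, no further model and no change to the sample size, since the models that give the direct effects are already planned.
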